### Inclusion criteria

Age ≥ 16 yearsRecurrent sore throats that fulfil current SIGN guidance [1] for elective tonsillectomySubject has provided written informed consent for participation in the study prior to any study specific procedures

### Exclusion criteria

Under 16 years of agePrevious tonsillectomyListed directly (i.e. added to waiting list without prior elective ENT outpatient appointment) during emergency admission (e.g. due to peritonsillar abscess/quinsy)nability to complete self-reported questionnaires and sore throat returnsTonsillectomy required for other indications:■ Primary sleep breathing disorder■ Suspected malignancy■ TonsillolithsEquipoise influenced materially by other clinical considerations:■ Pregnant or breastfeeding■ Bleeding diathesis■ Therapeutic anticoagulation

### Screening, recruitment and consent

The clinical team at the participating sites will identify patients who have been referred for consideration of tonsillectomy and will post a PIS along with their appointment letter. The information sheet will outline the study and how to watch the NATTINA information DVD on www.nattina.com. Screening will be performed on all patients who attend an ENT referral clinic visit with recurrent sore throat. Screening is defined as the assessment of the NATTINA eligibility criteria at the patient’s clinic visit. Potential participants who were posted a PIS will be shown the information DVD at their first clinic visit (unless already viewed online) and given the opportunity to discuss the study with the designated member of the research team. Inclusion and exclusion criteria will be checked and eligible patients invited to participate in the study.

Participants will be given reasonable time (minimum of 24 hours) to decide whether or not they would like to participate. Those who are not given a PIS before their clinic visit will receive a minimum of 24 hours to consider, and will be invited to attend a later appointment to consent. Eligible patients wishing to take part will be asked to provide written informed consent by signing and dating the Informed Consent Form (ICF), which will be witnessed, signed and dated by a member of the research team with documented, delegated responsibility to do so. The original signed consent form will be retained in the Investigator Site File, with a copy in the clinical notes and a copy provided to the participant.

Patients who, following screening, are eligible but decline to participate in NATTINA will be invited to provide anonymised baseline comparison data (age, gender, an estimate of number of sore throat days over the prior 6 months and a TOI 14 questionnaire [25]). This will allow an analysis of the comparability of the trial participants to the total pool of those referred at each of the nine sites. Declining patients will also be informed about the option to take part in an interview for the qualitative process evaluation.

### Randomisation

A blocked allocation method will be used to allocate participants to the 2 intervention groups; tonsillectomy versus conservative management, in a 1:1 ratio stratified by centre and severity. Randomisation will be administered centrally via NCTU using a secure web-based system, accessed by the Principal Investigator (PI) or delegated individual.

### Primary outcome measure

The number of sore throat days as reported through weekly ‘returns’ from the participants over a period of 24 months will be the primary outcome measure.

### Secondary outcomes measures

Responses on the TOI 14 [25] and STAR data to measure frequency, severity, health and economic impact of any sore throat episodes experiencedQOL as measured by the SF-12 [26] longitudinally during study follow-upThe number of adverse events, visits to the GP/walk-in clinic/A&E, prescriptions issued and additional interventions required as collected from GP records and other primary care linkage dataThe views and experiences of patients and clinicians regarding tonsillectomy and conservative management and how patient experience may shape any future research required

### Economic outcome measures

QALYs using the AUC method based upon SF-6D scores derived from the SF-12 [26] responses [27] measured at baseline, throughout the study and during any episodes of sore throat experiencedIncremental cost per sore throat day avoided from the perspective of the NHS and patients over 24 months to measure the cost-effectiveness

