## Background

The role of tonsillectomy in the management of adult sore throat remains uncertain, and despite demonstrable compliance with prevailing empirical guidance [1], UK regional variation in tonsillectomy rates persists [2]. The 2009 Cochrane review [3] identified only 1 evaluable adult trial with just 70 participants [4] followed up for only 90 days, and the review concluded that reasonable levels of evidence to support clinical decisions were only available for children. Currently there is evidence for increasing numbers of admissions for severe or complicated tonsillitis (e.g. peritonsillar abscess) as the number of tonsillectomy operations has fallen over the past decade in England [5]. The management of sore throats costs the National Health Service (NHS) over £120 million per annum – an estimated £60 million of this for general practitioner (GP) consultations and medical therapy [6]. From 2011–12 in England alone, secondary care costs included an estimated £10 million for bed usage and around £20 million in elective adult tonsillectomy [6].

The questions that patients, doctors and health policy makers wish to answer relate to the relative costs and benefits of tonsillectomy against conservative management (delayed surgery) and whether there can be more refined surgical indications to maximise such benefits, minimise the risks and make the best use of the scarce resources that are available.

Decision-making for tonsillitis is mostly undertaken in primary care where there may be the greatest potential for evolution in the patient pathway. Tonsillectomy is a painful procedure [7], which requires an average of 14 days off work [8, 9] and has a number of less common but intrusive complications [10] including changes in taste and tongue sensation [11, 12]. Thus, irrespective of its relative merits as a treatment, like all surgical intervention it needs to be weighed carefully against the alternatives.

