### Data collection and follow-up

All participants will be followed up for 24 months from the date of randomisation. Once consented, the participant will complete a baseline questionnaire booklet to be returned to NCTU. The participating site will then randomise the participant via the NCTU randomisation system. Participants randomised to immediate tonsillectomy will undergo surgery within 6–8 weeks of randomisation. All NATTINA participants will be prompted weekly by their preferred method of communication (short message service (SMS) message, Email or Interactive Voice Response (IVR) via telephone) to submit the number of sore throat days experienced in the previous 7 days, and requested to submit a STAR when they experience a sore throat. Through this the participant will provide details of the severity, use of any over-the-counter and prescription medications, the nature of any professional health care advice sought and the number of hours when unable to undertake usual activities (including work/studies). An additional SF-12 [26] will also be completed relative to the episode. The research nurse will contact participants randomised to the surgical arm at 1 and 2 weeks after their tonsillectomy to collect data concerning any adverse events. The participant will be asked to attend 2 further clinic visits and complete follow-up questionnaire booklets at 12 and 24 months, and to complete 2 other questionnaire booklets at home at 6-month and 18-month interim points. The 12-month clinic visit will allow participants in the conservative management group to be assessed on their willingness to remain in the deferred group. At their final 24-month visit these participants will be asked whether they wish to go forward for tonsillectomy. Adverse events and SAEs related to the study intervention will be collected throughout the duration of the study.

Consent will be sought to access participants’ GP health records in order to gather primary health care usage data at the end of their 24-month follow-up. Data collected will cover the participant’s 24-month follow-up and 12 months prior to randomisation, and will capture adverse events, number of contacts with primary and secondary health care services, prescribing information and other relevant material to support data retrieved from STARs and post-operative research nurse telephone calls (Table 1).

**Table 1 Tab1:** Data collection and time points

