### Statistical analysis

The primary outcome measure of the total number of sore throat days reported over the 24 months of follow-up will be analysed using negative binomial regression in order to compare any change between the NATTINA arms while adjusting for the stratification variables used – recruiting centre (as a random effect) and baseline severity (as a fixed effect). This analysis will be undertaken on an intention-to-treat basis; however, participants may switch over from conservative to surgical management. In the NATTINA design, although participants are asked to commit to ‘deferred surgery’, we anticipate that a number of participants will take up the opportunity to switch to surgery. The implication of such cross over, which typifies surgical trials, is that the intention-to-treat analysis will produce a very conservative estimate of the effect of tonsillectomy. We will, therefore, undertake a planned ‘as treated’ analysis with repeated measures corresponding to two periods of follow-up for those participants who cross over from medical management to tonsillectomy. The length of these follow-up periods will act as an exposure variable in the negative binomial regression.

QOL scores based on the SF-12 will be calculated according to the scoring manual at baseline and 6, 12, 18 and 24 months post randomisation. The scores will be analysed using models developed for longitudinal data. The dependent variable will be the QOL score for an individual patient at a particular occasion. Both variation between patients and variation between occasions nested within patients will be modelled as random effects with a normal distribution. Differences between groups and changes over time will be modelled as fixed effects. The analysis will be adjusted for the differences between strata.

The analysis of other secondary outcomes will follow a broadly similar strategy; repeated measures will be analysed using a random effects model with an appropriate error structure. Should data be found to be non-normally distributed, the use of transformations or non-parametric approaches will be considered.

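### No SF-12 is scheduled around surgery, so post-operative recovery enters the QALYs only if a participant files a sore throat return, and the article does not say whether recovery pain qualifies

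*Protocol article*

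**What the plan says.** The protocol article's Economic outcome measures section bases QALYs on the area under the curve of SF-6D scores from SF-12 responses "measured at baseline, throughout the study and during any episodes of sore throat". Table 1 gives the detail. The SF-12 is marked at baseline, at a sore throat episode, and at 6, 12, 18 and 24 months. Under Surgery only the case report form is marked.

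Data collection and follow-up adds three facts:

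- Timing of surgery: "Participants randomised to immediate tonsillectomy will undergo surgery within 6–8 weeks of randomisation".
- Post-operative contact: a research nurse contacts those randomised to surgery "at 1 and 2 weeks after their tonsillectomy to collect data concerning any adverse events". No SF-12 is mentioned.
- Episode route: all participants are prompted weekly and "requested to submit a STAR when they experience a sore throat". With that return, "An additional SF-12 [26] will also be completed relative to the episode".

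The Background describes tonsillectomy as painful, an operation "which requires an average of 14 days off work".

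The Statistical analysis section states that "QOL scores based on the SF-12 will be calculated according to the scoring manual at baseline and 6, 12, 18 and 24 months", so the longitudinal quality-of-life analysis rests on the fixed time points. The Economic analysis section repeats the area-under-the-curve method and mentions no separate treatment of the post-operative period.

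**The concern.** Recovery from tonsillectomy is a foreseeable loss of health with a known date, caused by one of the two treatments compared. The fixed SF-12 schedule steps over it. The only other route is the STAR, which depends on the participant deciding that post-operative throat pain is a sore throat and then filing a return. The article neither includes nor excludes such pain, so two participants at the same site could reasonably act differently.

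At stake are the QALY difference and the cost per QALY. Whether a real cost of surgery is counted, missed or over-counted would depend on an undefined reporting choice. An analysis plan can decide how to weight scores that exist, but it cannot recover responses that were never requested.

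**Working it through.** **Inputs from the article.** Surgery 6 to 8 weeks after randomisation; 14 days off work (Background); target difference 3.6 sore throat days, SD 10.8, 224 per group (Sample size calculation).

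**Assumed, not in the article.** A utility decrement *u* of 0.1 to 0.3 during recovery, and 14 days off work as a proxy for the length of recovery.

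**1. The plan's own figure.** The article gives no QALY figure; the nearest benchmark is the 3.6-day target. Its effect size is 3.6/10.8 = 0.33. With 90% power and a two-sided type 1 error of 2.5%, this gives 224 per group, as stated. Allowing for 25% loss, 448/0.75 = 597.3, so 598, consistent with 600.

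**2. Where recovery falls.** Fourteen days after surgery at week 6 to 8 ends at week 8 to 10. The next scheduled SF-12 is at about week 26, which is 16 to 18 weeks later. On scheduled scores alone, the curve runs straight from baseline to month 6 and recovery has no weight.

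**3. Loss if not captured.** Loss per operation = *u* × 14/365.25.

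| *u* | 14-day recovery | 3.6 days at the same *u* |
|---|---|---|
| 0.1 | 0.0038 | 0.0010 |
| 0.2 | 0.0077 | 0.0020 |
| 0.3 | 0.0115 | 0.0030 |

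The ratio is 14/3.6 = 3.9 if a recovery day and a sore throat day carry the same decrement. It is a benchmark of scale, not a predicted bias.

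**4. Partial capture.** If a fraction *p* of operated participants file a STAR and its score is weighted by episode length, the missed loss is (1 − *p*) × *u* × 14/365.25. At *p* = 0.5 it is 0.002 to 0.006; at *p* = 1 it is zero.

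**5. Cross-over.** If a fraction *c* of controls are also operated on and nothing is captured in either arm, the between-arm error is (1 − *c*) × *u* × 14/365.25. The article gives no rate. At an illustrative *c* = 0.25 it is 0.003 to 0.009.

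**6. One STAR score joined by straight lines.** A single score lower by *u* between baseline and month 6 forms a triangle of area *u* × 0.5/2 = 0.25*u* years, wherever in the interval it falls. That is 0.025 to 0.075 QALY, against a true loss of 0.004 to 0.011. The ratio is 0.25/(14/365.25) = 6.5, and the error is against tonsillectomy.

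**7. The same trap with two post-operative scores.** Let scores at 1 and 2 weeks both be lower by *u*, with month 6 at day 183. Straight-line joining gives (183 − 7)/2 + 7 = 95 decrement-days against 14, a ratio of 6.8. Collecting the scores is therefore not enough; the weighting matters too.

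**The case against.** The strongest reply is that the STAR route already covers recovery. Every participant is prompted weekly to 24 months, nothing exempts the weeks after surgery, and throat pain after a throat operation is a sore throat on an ordinary reading. This stands as far as direction goes. A reader might infer from the empty Surgery cell that the QALYs are biased towards tonsillectomy. The article does not support that: with full capture and duration weighting the error is zero, and with straight-line joining it reverses. What remains is that capture rests on an undefined and voluntary step.

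The size can also be challenged:

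- Days off work are not days at a measured utility loss.
- The 3.9 ratio needs a common decrement.
- The 3.6 days is a detectable difference in the primary outcome, not an expected QALY gain; the 6-monthly SF-12 scores may show gains beyond avoided sore throat days.
- If post-operative pain is reported in the weekly returns, the 3.6 days may already be net of it, and the same people would be asked for a STAR.
- Controls who cross over share the loss.

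All of this is fair, and the range should be read as conditional.

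Finally, this is a condensed article. STAR instructions, the content of the surgical case report form and the weighting of scores may sit in documents not shown, and the article promises deterministic sensitivity analyses of key uncertainties. The weighting detail is accordingly not a finding. The SF-12 schedule is one, because Table 1 sets it out explicitly, and a sensitivity analysis could only substitute an assumed decrement for data never collected.

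**Conclusion.** The point holds as a gap in data collection: no SF-12 is tied to surgery, the post-operative contacts are described as collecting adverse events only, and the single remaining route is not defined for post-operative pain.

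Its consequence is conditional. With no capture, the QALY difference can favour tonsillectomy by about 0.004 to 0.011 per operated participant, less after control cross-over. That is enough to change the sign of a small QALY difference. With a single STAR score joined by straight lines, the loss is overstated about 6.5-fold in the other direction. Both figures rest on the assumed decrement of 0.1 to 0.3 and a 14-day recovery. A settled bias in favour of surgery should not be inferred.

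The matter affects the economic outcomes, not the primary clinical comparison. It should be corrected, because prevention is cheap and the missing responses cannot be recovered later.

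**What to change.** - Add the SF-12 to the 1- and 2-week post-operative contacts for every participant who has a tonsillectomy, including those who cross over from conservative management, and mark it under Surgery in Table 1.
- State that the resulting decrement applies over the length of recovery only. Do not enter these scores as ordinary points joined by straight lines to baseline and month 6.
- State whether post-operative throat pain counts as a sore throat episode, and use one source for the recovery weeks so that a STAR from the same period is not counted twice.

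Cost: a schedule amendment and a slight extra burden on participants. For those randomised to surgery the contacts already exist. The article states no such contact for cross-overs, so a few calls would be added. Scores taken at a nurse contact may also differ from questionnaire-booklet scores because of the mode of administration; this should be acknowledged when the results are reported.

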### Data collection and follow-up

All participants will be followed up for 24 months from the date of randomisation. Once consented, the participant will complete a baseline questionnaire booklet to be returned to NCTU. The participating site will then randomise the participant via the NCTU randomisation system. Participants randomised to immediate tonsillectomy will undergo surgery within 6–8 weeks of randomisation. All NATTINA participants will be prompted weekly by their preferred method of communication (short message service (SMS) message, Email or Interactive Voice Response (IVR) via telephone) to submit the number of sore throat days experienced in the previous 7 days, and requested to submit a STAR when they experience a sore throat. Through this the participant will provide details of the severity, use of any over-the-counter and prescription medications, the nature of any professional health care advice sought and the number of hours when unable to undertake usual activities (including work/studies). An additional SF-12 [26] will also be completed relative to the episode. The research nurse will contact participants randomised to the surgical arm at 1 and 2 weeks after their tonsillectomy to collect data concerning any adverse events. The participant will be asked to attend 2 further clinic visits and complete follow-up questionnaire booklets at 12 and 24 months, and to complete 2 other questionnaire booklets at home at 6-month and 18-month interim points. The 12-month clinic visit will allow participants in the conservative management group to be assessed on their willingness to remain in the deferred group. At their final 24-month visit these participants will be asked whether they wish to go forward for tonsillectomy. Adverse events and SAEs related to the study intervention will be collected throughout the duration of the study.

Consent will be sought to access participants’ GP health records in order to gather primary health care usage data at the end of their 24-month follow-up. Data collected will cover the participant’s 24-month follow-up and 12 months prior to randomisation, and will capture adverse events, number of contacts with primary and secondary health care services, prescribing information and other relevant material to support data retrieved from STARs and post-operative research nurse telephone calls (Table 1).

**Table 1 Tab1:** Data collection and time points

Measure	Baseline	Weekly (baseline to 24-month FU)	Sore throat episode	Surgery	6-month FU	12- month FU	18- month FU	24- month FU
'About You' Questionnaire	X							
'Value of Avoiding a Sore Throat Day' Questionnaire	X							
TOI 14	X				X	X	X	X
SF-12	X		X		X	X	X	X
Health Service Utilisation Questionnaire	X				X	X	X	X
Participant Time and Travel Questionnaire							X	
Comparison data (declining patients)	X							
Weekly alert		X						
Sore Throat Alert Returns (STAR)			X					
CRF	X			X	X	X	X	X
GP Linkage Data								X

*CRF* Case Report Form, *FU* follow-up, *SF-12* Short Form 12 Health Survey, *TOI 14* Tonsillectomy Outcome Inventory 14

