### Study compliance and withdrawal

Where feasible, visit windows of ±6 weeks should ensure sufficient time is offered to facilitate scheduling appointments; non-attendance for study visits will prompt follow-up by telephone. Participants may also be contacted via telephone by the research nurse at the participating site to remind or encourage them to return questionnaires or weekly alerts. Source data verification will be performed by the Trial Manager at each participating site.

Participants will have the right to withdraw from the study at any time for any reason, and without giving a reason. The investigator will also have the right to withdraw participants from the study intervention if he/she judges this to be in their best interest. At the participants’ request, those in the conservative management arm will be able to cross over into the surgical arm or withdraw completely with no further data collected. Participants in the tonsillectomy arm will be able to either withdraw completely or cross over to the conservative management arm before surgery has occurred.

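### The 1- and 2-week post-operative adverse event calls are tied to randomised arm, not to the operation, so controls who switch to tonsillectomy have no scheduled early contact

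*Protocol article*

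**What the plan says.** The rule for the calls is in the protocol article under Data collection and follow-up: the "research nurse will contact participants randomised to the surgical arm at 1 and 2 weeks after their tonsillectomy". The purpose of these calls is to gather adverse event data. Eligibility for a call is therefore set by allocation.

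Two other sections bear on this. Study compliance and withdrawal provides that, on request, "those in the conservative management arm will be able to cross over into the surgical arm or withdraw completely with no further data collected". Statistical analysis says of the control arm that "we anticipate that a number of participants will take up the opportunity to switch to surgery", and plans an as-treated analysis of sore throat days for that reason.

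Other adverse event collection is not restricted by arm:

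- Data collection and follow-up states: "Adverse events and SAEs related to the study intervention will be collected throughout the duration of the study".
- GP records, retrieved with consent at the end of follow-up, "will capture adverse events, number of contacts with primary and secondary health care services, prescribing information". The same section describes them as supporting the STARs (Sore Throat Alert Returns) and the post-operative calls.
- Table 1 ("Data collection and time points") marks a CRF at Surgery and at 6, 12, 18 and 24 months, and a Health Service Utilisation Questionnaire at the same four follow-up points.

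**The concern.** A participant's randomised arm never changes. A control who has a tonsillectomy at, say, month 9 is still not someone randomised to surgery, so the rule as written gives that patient no call. The same operation is then followed with different intensity in the two arms, and the difference depends on allocation.

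What is at stake is the count of early complications. Events that a patient would mention to a nurse at 1 or 2 weeks may otherwise surface only at the next follow-up point or in the GP record, or not at all. Any complication count that uses the calls could then be too low per operation when all tonsillectomies are pooled, and the arms would not be comparable. The article says safety data will not be tested statistically. That does not remove the problem, because unequal ascertainment also biases descriptive counts.

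**Working it through.** **1. Does any other scheduled contact fall in the first weeks after a switcher's operation?**

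| Route | Applies to switchers? | Timed to the weeks after their operation? |
|---|---|---|
| Nurse calls at 1 and 2 weeks | No, as worded | Yes |
| Surgery CRF | No arm limit shown | Marked at surgery, not after it |
| CRF at 6, 12, 18, 24 months | Yes | No, timed from randomisation |
| Health Service Utilisation Questionnaire | Yes | No, same four points |
| Weekly prompt | Yes | Falls every week, but asks only for number of sore throat days |
| STAR | Yes | Triggered by a sore throat; covers severity, medication, advice sought and hours lost |
| Study-wide adverse event and SAE collection | Yes | No method or schedule given in the article |
| GP records | Yes, with consent | No, retrieved once at the end of follow-up |

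Switchers are covered by several routes. None of them is a scheduled adverse event enquiry in the two weeks after their operation. A complication without sore throat, such as the changes in taste and tongue sensation that the Background mentions, need not trigger a STAR.

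**2. How many operations could be affected?**

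The article gives no figure for adverse event collection and no switch rate, so there is no stated figure to reproduce. The inputs are:

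- 600 participants, allocated 1:1 (Sample size calculation; Randomisation), so 600 / 2 = 300 per arm.
- Switch rate *c* among controls: assumed, 10% to 40%.
- All 300 surgical-arm participants are operated on: assumed.

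Operations without a scheduled call = 300 × *c*. Share of all operations = 300*c* / (300 + 300*c*) = *c* / (1 + *c*).

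| *c* (assumed) | Operations without a call | All operations | Share |
|---|---|---|---|
| 10% | 30 | 330 | 9% |
| 20% | 60 | 360 | 17% |
| 30% | 90 | 390 | 23% |
| 40% | 120 | 420 | 29% |

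If some surgical-arm participants are not operated on, which the withdrawal section allows, the counts in the second column stay the same and the shares rise.

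**3. Which results does this reach?**

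The primary outcome comes from weekly returns in both arms, so neither it nor the sample size is touched. For the adverse event outcome, the secondary objectives name STAR data supported by primary care linkage, and the secondary outcome list names GP records and other linkage data. Both sources serve both arms, and neither section names the calls. The effect is therefore confined to complication counts that draw on the calls.

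**The case against.** The strongest reply is that switchers are not left unobserved. Study-wide collection of intervention-related events, the Surgery and follow-up CRFs, the utilisation questionnaires and the GP records all apply to them. This stands. A reader might infer that complications in switchers are not actively collected, or that the calls are the only active collection. The documents do not support either reading. What is missing is early contact timed to the operation.

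A reader might also infer that the listed adverse event outcome is understated in controls under intention to treat, or that the cost results are distorted. Neither is shown. The named sources for that outcome apply to both arms, and the economic section takes resource use from CRFs and participant questionnaires, not from the calls. No summary of safety by treatment received is specified either; the as-treated analysis is described for sore throat days.

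The closing words of the withdrawal sentence might suggest that data collection stops for switchers. They describe complete withdrawal, which is the alternative to crossing over.

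Finally, this is a condensed article. The full protocol, which is not shown, may extend the calls to any tonsillectomy, and the phrase about crossing into the surgical arm makes it plausible that sites would treat switchers that way. That lowers confidence about what happens in practice. It does not dispose of the point, because the article states a specific rule, and that rule does not fit the switching the article itself expects.

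**Conclusion.** The point holds in a limited form. As written, the rule makes scheduled early follow-up of the same operation depend on allocation. Switchers' early post-operative events may be recorded later and less completely, and counts that use the calls could be too low per operation and not comparable by arm. Under the assumptions above, 30-120 operations (9-29% of all) would lack two scheduled calls. That is a count of operations without a call, not of events missed; the documents give no basis for estimating the latter. This is a modest matter of safety ascertainment, worth correcting because the correction is cheap.

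**What to change.** In Data collection and follow-up, replace the trigger so that the 1- and 2-week calls go to every participant who has a tonsillectomy during the 24-month follow-up, whichever arm they were randomised to. Tabulate operative adverse events by operation received as well as by allocated arm. If the full protocol already extends the calls to switchers, the article's sentence need only be aligned with it.

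The cost is one sentence, two short calls per switcher by the research nurse already making such calls (60-240 calls over the trial at the assumed 30-120 switchers, 2 × 30 to 2 × 120), and one more table. It changes data collection only. The article reports that recruitment had not yet begun, so the change could apply from the first participant.
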